### Design and setting

The study is a feasibility randomized controlled trial (RCT) using a wait list control trial design. Due to COVID-19 restrictions, this study has been adapted from in-person delivery to telehealth delivery via Zoom. The first 48 people to meet the eligibility criteria will be randomly allocated to receive EFMT immediately, or in 8 weeks from time of baseline assessment (1:1 allocation ratio). Data will be collected by a blinded to group research assistant (RA) at baseline (T1), 8 weeks following baseline (T2), and 16 weeks following baseline (T3). Participants will be recruited from primary care clinics and community organizations that provide support to older adults. The principal investigator (PI)/facilitator of the EFMT groups will be blinded to the results of outcome assessments until the end of the intervention phase of the study. The PI is a registered psychotherapist certified in delivering EFMT and will facilitate all groups.

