### Interventions

#### Comparators

The comparator will be no treatment (treatment as usual) for the controlled wait list group. All participants will receive the intervention. All participants will receive T1, T2, and T3 assessments within 7–10 days of each timepoint.

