### Sample size justification

A sample size of 48 participants will allow for intervention group sizes of six participants and wait listed control group sizes of six participants. There will be four blocks of participants, with 12 participants in each block, and groups of six participants. This will result in 24 participants per arm. Small sample sizes of 10–20 participants or more are appropriate for pilot testing of adherence to interventions and this study will exceed those numbers, thereby allowing for attrition [48, 49]. There are also pragmatic considerations to selecting the sample size for this study [50], which include planning to complete the study within a year with limited funding. The study will not be powered to detect significant changes on the secondary outcomes. As COVID-19 protocols prohibit groups meeting in person, this study has moved to Zoom, an online privacy protected platform [51]. Other COVID-19 adjustments pivots required will be shorter meetings of 1.5 h to avoid Zoom fatigue and smaller group sizes [40]. This will be sufficient to meet the study’s primary objectives of recruitment, retention, and completion rates to determine whether a large study is warranted.

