#### Collection of information at T3

All participants will be contacted by telephone by the RA to re-administer the GAI, PSQI, and MMSQ and to collect data on extraneous life events, within 1 week of completion of the intervention for the wait list control group. The RA will attempt to collect data from all participants whether or not all sessions are attended.

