### Statistical methods

Data entry will be conducted by the RA. Data analysis will be conducted by the PI at the end of the study using SPSS V27 [68]. All data will be examined by running frequencies on each variable to determine if values are missing or out of range. Possible errors will be compared to raw data and corrected as necessary to ensure accuracy [67]. As is recommended for pilot feasibility studies, the following descriptive statistics will be used: for continuous variables, minimum, maximum, mean, median, mode standard deviation, skewness, and kurtosis; if continuous variables are skewed, non-parametric descriptive statistics will be reported; for categorical variables, frequencies will be used [69, 70]. Graphical displays such as histograms or boxplots will be presented to demonstrate and better understand the central tendency and dispersion of the data [67]. Recruitment, enrollment, and retention rates will be calculated. Rates of attendance and adherence to each component of the intervention will also be calculated to determine acceptability.

To examine whether there have been potential changes in the secondary outcomes, descriptive statistics will be used to analyze and present demographic and baseline data. Categorical and ordinal data will be compared using chi-square. Continuous data will be compared using a *t*-test. The mean change in the intervention group and wait list control group outcomes will be compared post intervention (T3) using an independent samples *t*-test, and Cohen’s *d* will be calculated for effect size [67]. Data from each of the groups will be combined to form a larger sample size to evaluate the effect of the intervention. Analysis of pooled data will be conducted using a paired sample *t*-test and Cohen’s *d* to examine the intervention effect over baseline measures. Change over time for the intervention group from T1 to T2 to T3 will be calculated by using repeated measures ANOVA to determine if change has occurred and/or is maintained in the intervention group.

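### The pooled paired analysis does not name its timepoints; with baseline read as T1, it counts the wait-list arm's eight untreated weeks as intervention effect

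*Protocol article*

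**What the plan says.** Design and setting fixes the assessments for all participants "at baseline (T1), 8 weeks following baseline (T2), and 16 weeks following baseline (T3"). Participants are "randomly allocated to receive EFMT immediately, or in 8 weeks from time of baseline assessment (1:1 allocation ratio"). Under Comparators the waiting period is untreated and everyone is treated in the end: "The comparator will be no treatment (treatment as usual) for the controlled wait list group. All participants will receive the intervention". The section on collection at T3 places that assessment "within 1 week of completion of the intervention for the wait list control group", so T3 is the wait-list arm's first post-treatment measurement.

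After describing a between-arm t-test at T3, Statistical methods combines the arms: "Data from each of the groups will be combined to form a larger sample size to evaluate the effect of the intervention". It continues: "Analysis of pooled data will be conducted using a paired sample *t*-test and Cohen’s *d* to examine the intervention effect over baseline measures". Neighbouring sentences carry timepoint labels; this one does not. Nowhere is baseline redefined as T2 for the wait-list arm.

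**The concern.** An analyst who follows the text takes baseline to be T1. The immediate arm's first before-after pair then spans 8 weeks, all of them during EFMT. The wait-list pair spans 16 weeks, and the first 8 precede any treatment. Whatever happens to anxiety, sleep or memory during the wait enters a quantity described as the effect of the intervention.

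The planned between-arm test offers no correction, because it is placed at T3, when both arms have been treated. The pooled analysis is presented as the one with the larger sample. The Discussion says that findings will inform sample size calculations for a definitive trial, so a displaced Cohen's d could be carried into that planning.

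**Working it through.** **Inputs from the protocol**
- T1 is baseline, T2 is at 8 weeks and T3 at 16 weeks (Design and setting).
- Wait-list EFMT starts 8 weeks after the baseline assessment, with no treatment before then (Design and setting; Comparators).
- The wait-list post-treatment value is T3 (Collection of information at T3).
- Sample size: 48 people, enrolled as four sets of 12, giving 24 in each arm (Sample size justification).
- Retention criterion of 65% (Feasibility and acceptability outcomes).

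**Not given:** the untreated change, the SD of change, and any alpha or effect size for the pooled test. Values used for these below are assumptions.

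**Step 1: the plan's own figure.** 4 × 12 = 48, and 48 / 2 = 24 per arm. This reproduces. At 65% retention, 0.65 × 48 = 31.2; 32 is used as an even approximation.

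**Step 2: algebra.** Count improvement as positive. Let a be the immediate arm's mean change from T1 to T2, b the wait-list mean change from T2 to T3, and u the wait-list mean change from T1 to T2. With equal numbers per arm:
- wait-list pair T1 to T3: pooled mean = (a + u + b) / 2
- wait-list pair T2 to T3: pooled mean = (a + b) / 2
- difference = u / 2

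**Step 3: size under assumed u.** Set a = b = 0 and the SD of change to 1 in both arms, and use a two-sided 5% paired t-test with 40,000 simulated trials.

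| u (SD) | Shift u/2 (SD) | Rejection, n = 48 | Rejection, n = 32 |
|---|---|---|---|
| 0 | 0 | 4.9% | 4.8% |
| 0.2 | 0.10 | 10.4% | 8.3% |
| 0.3 | 0.15 | 17.0% | 12.5% |
| 0.5 | 0.25 | 37.4% | 25.9% |
| 0.8 | 0.40 | 72.7% | 53.0% |

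The row u = 0 is also the result of pairing the wait list from T2 when nothing changes during EFMT. If u is negative (worsening while waiting), the shift has the same size and the benefit is understated.

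**Step 4: what the pairing does and does not remove.** Assume a natural improvement of 0.3 SD in both arms, all in the first 8 weeks.
- EFMT effect 0: from T1, (0.30 + 0.30) / 2 = 0.30; with wait-list T2, (0.30 + 0) / 2 = 0.15.
- EFMT effect 0.5 SD: from T1, (0.80 + 0.80) / 2 = 0.80; with wait-list T2, (0.80 + 0.50) / 2 = 0.65.

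The gap is 0.15 SD both times, which is u/2. The remaining 0.15 SD is natural change in the immediate arm during EFMT, and re-pairing does not remove it. If the same 0.3 SD is spread evenly over 16 weeks, u = 0.15. With no EFMT effect the figures are then (0.15 + 0.30) / 2 = 0.225 and (0.15 + 0.15) / 2 = 0.15, a gap of 0.075 SD.

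**Step 5: possible consequence.** Taking these d values at face value for a later two-arm trial (two-sample t-test, two-sided 5%, 80% power), d = 0.80 needs 26 per arm, 0.65 needs 39 and 0.50 needs 64.

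**The case against.** The strongest reply is that Statistical methods never writes T1 in the pooled sentence. Pooling in order to evaluate the intervention is compatible with each arm's own before and after values, and a condensed article may leave the exact pairs to a fuller plan. This stands in part. A reader might infer that the protocol prescribes T1 to T3 for the wait list; it does not say so in terms. What it does fix is the pooling, the test, the interpretation and a reference to baseline, and the only baseline it defines is T1. On the kinder reading the pairs still have to be stated.

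A reader might also infer that the pooled effect must be inflated, because anxious people tend to improve after enrolment. The documents do not establish that direction. The Eligibility criteria section contradicts itself on the GAI: it treats 10 as indicating anxiety, yet admits scores of 10 or below. The Background reports anxiety rising with COVID-19, so worsening during the wait is possible.

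Nor may the whole 0.30 SD of the illustration be charged to the choice of baseline. Only half of it is, and the 0.3 SD is itself an assumption.

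Finally, the analysis is secondary, the trial is not powered for it, and the Discussion disclaims hypothesis testing. All of that is correct and limits the weight of the point. It does not make the reference point right.

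**Conclusion.** The point holds as an unspecified pairing which, under the protocol's only definition of baseline, brings about 8 untreated wait-list weeks into the pooled estimate. The displacement is u/2 with equal numbers per arm: 0.15 SD if u is 0.3 SD, nothing if u is zero, and an understatement if participants worsen while waiting. The sizes rest on assumed values of u, and the rejection rates also on unit SD of change and no mean change during EFMT.

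Severity is moderate. Recruitment, enrolment, retention and adherence are unaffected, and no feasibility threshold uses the pooled d. It is still more than missing detail, because the text as written leads to a different estimate from the one its stated purpose calls for, and that estimate may inform the size of a definitive trial.

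**What to change.** In Statistical methods:
- Define the pooled pairs by arm: T1 to T2 for the immediate arm, T2 to T3 for the wait-list arm.
- State that the wait-list T2 assessment is taken before that arm's first session. This is not guaranteed now: T2 may fall within 7–10 days of its timepoint (Comparators) or up to a week after the first intervention ends (Collection of information at T2), while wait-list EFMT starts 8 weeks after baseline.
- Report the wait-list T1-to-T2 change beside the pooled result as the untreated reference.
- Call the pooled result uncontrolled pre-post change. The present purpose, "to examine the intervention effect over baseline measures", claims more than a paired test without a control arm can show, even after re-pairing.

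T2 is already planned for everyone, so no new measurement is needed. The cost is a few sentences, some discipline over the timing of wait-list T2 calls, the loss from the pooled set of any wait-list participant without a T2 value, and possibly a smaller pooled effect size.

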**Methods:**

This pilot feasibility randomized controlled trial will use a wait list control trial design. Due to COVID-19 restrictions, we will use telehealth delivery via Zoom rather than in-person delivery. The first 48 people to meet the eligibility criteria will be randomly allocated to either receive EFMT immediately, or in approximately 8 weeks time from enrollment (1:1 allocation ratio). Data will be collected at baseline, 8 weeks following baseline, and 16 weeks following baseline. The primary outcomes will determine the feasibility of the intervention based on recruitment, enrolment, retention, and adherence to all components of the intervention. The secondary outcome will be changes to anxiety over time.

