## Methods

### Participants, interventions, and outcomes

This study aims to evaluate the feasibility of EFMT for community dwelling adults 55 and older with symptoms of anxiety. The secondary outcomes will be measurements of changes to anxiety, sleep, and subjective memory functioning over time.

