### Outcome collection and measures

*Aim 1*. Determine if participants can be recruited, enrolled and retained

Recruitment, enrollment and retention data will be used to evaluate feasibility. Data will be gathered and measured on the number of potential participants referred and screened for eligibility, participants meeting eligibility requirements, participants enrolled, and participants completing the intervention. Recruitment and enrollment will be considered feasible if 70% of the total number of potential participants meeting eligibility requirements consent to enroll [44], and if 48 participants can be enrolled within a 3-month period (16 participants recruited per month). Retention will be considered feasible if 65% of participants complete data collection at both timepoints [45].Variables such as changes to medications, beginning, or stopping mental health counseling and significant life events will be tracked by the RA at T3 data collection timepoint. Extraneous variables will be important to gather to identify other potential reasons for changes to secondary outcomes aside from EFMT.

*Aim 2*. To determine if participants can adhere to all components of the intervention

Adherence will be used to measure acceptability. The intervention will be considered acceptable if 70% of participants attend of a minimum of six meetings [44]. As well, acceptability for measures of adherence to meditation, journaling, and reporting will be gathered through PI observation and documentation. Adherence to these components will be considered acceptable if the majority (75% or more) of participants appear to be meditating, journaling and actively report their meditations. Participants will not be required to practice between meetings; however, data will be gathered on the frequency and duration of home practice meditation and journaling to explore whether there is a relationship to outcomes. Participants will complete weekly reporting forms to be emailed to the PI. The PI will keep an observational diary noting what works well and perceived areas of challenge.

*Aim 3*. To determine the secondary objective of whether participants who receive the intervention potentially have decreased levels of anxiety compared to those participants who do not receive the intervention, the GAI will be used [35]. Outcome measures will be collected using the GAI at T1, T2 and T3.

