To determine the secondary objectives, the extent to which participants who receive the intervention potentially experience changes to sleep quality and subjective memory functioning compared to participants who do not receive the intervention, the Pittsburgh Sleep Quality Index (PQSI) and the Multifactorial Memory Questionnaire (MMQ) will be used [46, 47] (Fig. 1).

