### Data collection and management

#### Collection of information at T1

T1 data collection will be conducted by the RA, a master’s level researcher trained by the PI in the administration of scoring of the three assessments to be administered. The RA will administer the GAI. The GAI has been validated for use in community dwelling adults over the age of 60, with excellent test-retest reliability of *r* = .91 to .95 [35, 53–55]. This anxiety scale was selected because it is commonly used in a range of clinical settings [56]. The RA will administer the PSQI and the MMQ [46, 57]. The PQSI is a sleep quality and sleep disturbance assessment validated for use with community dwelling older adults [46]. This measure was selected because sleep complaints are frequently associated with anxiety [58]. The PQSI is a simple 19 item subjective measure of sleep quality and patterns of sleep using a 0 to 3 Likert scale [59]. The PQSI has been demonstrated to have excellent test-retest reliability (*r* = .85–.87) and internal consistency of Cronbach’s *a* of .80–.83 [46, 60, 61]. The MMQ is a 21-item brief self-report assessment of subjective memory ability validated for use with community dwelling older adults [57, 62]. This assessment measures satisfaction, ability and strategy use in memory. It was chosen because older adults with anxiety frequently report problems with memory [4, 5, 15–17]. The MMQ has high test-retest reliability over time (.86–.95) [62, 63]. Cronbach’s *a* internal consistency is good at .87 to .93 [57, 62, 64].

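### No planned analysis compares EFMT with no treatment: the only between-arm test is at T3, after the wait list arm has been treated, and the other two have no control

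*Protocol article*

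**What the plan says.** All places are in the protocol article.

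- **Aims.** The primary outcomes concern feasibility: "The primary outcomes will determine the feasibility of the intervention based on recruitment, enrolment, retention, and adherence to all components of the intervention". Each secondary objective (Objectives) is worded as a comparison between those who receive the intervention and those who do not. The abstract's Discussion says the results will determine feasibility and potential effectiveness for late-life anxiety, with no treatment as the comparison.
- **Secondary outcomes.** The abstract names one: "The secondary outcome will be changes to anxiety over time". The main text names three: "The secondary outcomes will be measurements of changes to anxiety, sleep, and subjective memory functioning over time".
- **Data.** For anxiety, "Outcome measures will be collected using the GAI at T1, T2 and T3". Collection of information at T2 has all participants in both arms called again for all three scales. Collection of information at T3 places that call after the wait list arm has finished its own course.
- **Analyses (Statistical methods).** There are three: an independent samples t-test of mean change between arms, with T3 given as the timepoint; a paired t-test on pooled data, introduced with "Data from each of the groups will be combined to form a larger sample size to evaluate the effect of the intervention"; and an analysis of the immediate arm alone, "using repeated measures ANOVA to determine if change has occurred and/or is maintained in the intervention group".
- **Disclaimers.** Sample size justification says the study is not powered for the secondary outcomes. The closing Discussion says it will not examine hypothesis testing.

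**The concern.** A wait list design gives one randomised comparison of treated with untreated people. It lasts until the wait list arm starts treatment, which here means T2. The article collects data at that point but plans no between-arm analysis there. It places the between-arm test at T3, when both arms have had EFMT, and gives the language of intervention effect to an analysis without controls.

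At stake is the statement on potential effectiveness. If EFMT works and the gain lasts, the T3 contrast tends towards zero and the trial may look negative between arms. If EFMT does nothing but participants improve anyway (regression to the mean after selection on symptoms, or easing of pandemic conditions), the pooled test can be positive and be read as an effect. The closing Discussion says the findings will inform sample size calculations for a definitive trial. Cohen's d is planned for both the between-arm and the pooled analysis, and neither estimates the treated-versus-untreated difference that such a calculation needs.

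**Working it through.** **1. Sample size.** 4 blocks × 12 = 48, or 24 per arm, which reproduces the article's figure. With the article's 65% retention benchmark, 24 × 0.65 = 15.6, about 16 per arm. The analysed range is therefore 16 to 24 per arm, or 32 to 48 pooled.

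**2. What each analysis estimates.** Let δ be the effect of EFMT just after the course, r the share retained 8 weeks later, and D2 and D3 the change common to both arms by T2 and T3.

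| Contrast | Immediate arm | Wait list arm | Estimates |
|---|---|---|---|
| Between arms, T1 to T2 (not planned) | D2 + δ | D2 | δ |
| Between arms, T1 to T3 (planned) | D3 + rδ | D3 + δ | (r − 1)δ |
| Pooled pre-post (planned), each arm's own post-course score | D2 + δ | D3 + δ | δ + average of D2 and D3 |
| One-arm ANOVA (planned) | D2 + δ, D3 + rδ | none | effect and drift mixed |

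With full retention (r = 1) the planned T3 contrast has expectation zero however large δ is. With partial retention it points the wrong way. The pooled analysis and the ANOVA cannot separate δ from D. Only the T1-to-T2 contrast removes D and keeps δ.

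**3. Size of the drift problem for the pooled anxiety test.** Assumptions, none given in the article: two-sided alpha 0.05, equal SD of 1 at each time, correlation over time 0.6, no EFMT effect, and a common improvement of 0.2 or 0.3 SD by T2 that then holds.

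- SD of change = √(2 × (1 − 0.6)) = 0.894.
- Noncentrality = drift / 0.894 × √n.

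| Drift (SD) | Pooled n | Noncentrality | Chance of a positive test |
|---|---|---|---|
| 0.2 | 32 | 1.265 | 0.23 |
| 0.2 | 48 | 1.549 | 0.33 |
| 0.3 | 32 | 1.897 | 0.45 |
| 0.3 | 48 | 2.324 | 0.62 |

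Simulation under the same assumptions gave 23–33% at 0.2 SD and 46–63% at 0.3 SD, in agreement.

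**4. A between-arm test under the same drift.** The common change cancels. In simulation with 24 per arm and no EFMT effect, the anxiety between-arm test was positive in 4.4% of trials at both 0.2 and 0.3 SD. That run used T3. With no EFMT effect, the same cancellation applies at T2.

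**5. Precision of the T2 contrast, same assumptions.** Standard error = 0.894 × √(2/m) for m per arm.

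- m = 24: 0.258, so the 95% half-width is 2.013 × 0.258 = 0.52 SD.
- m = 16: 0.316, so the 95% half-width is 2.042 × 0.316 = 0.65 SD.

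The interval is wide, as the article's own statement about power implies, but it is centred on the right quantity.

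**The case against.** The strongest reply is that this is a feasibility pilot. Its primary outcomes are feasibility measures with numeric thresholds, Sample size justification ties the decision on a larger study to recruitment, retention and completion, and power and hypothesis testing are disclaimed. The secondary aims are hedged as potential changes, and Outcome collection and measures plans to record medication changes, counselling and life events as other explanations.

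Much of this stands. It disposes of a stronger reading that a reader might infer: three scales times three analyses make nine tests, more if the memory questionnaire's areas are scored separately, so a claim could rest on whichever is positive. The documents do not support that as the main point. No confirmatory claim hangs on these tests. The abstract names anxiety alone as the secondary outcome, its statement of potential effectiveness concerns anxiety, and the GAI has its own aim. Any family-wise error rate would need an assumed alpha and assumed correlations, and the number of memory scores is not stated. Ranking of secondary outcomes may also sit in an analysis plan that is not shown.

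The disclaimers do not cure the rest. A disclaimer of hypothesis testing sits awkwardly beside planned significance tests, and it does not turn an uncontrolled change into a treatment effect. Recording life events at T3 is not a control group. The T3 label may be a slip for T2, but it is what the text states and it needs correcting either way. The general sentence on comparing continuous data by t-test follows the sentence on demographic and baseline data and names no follow-up time. If change were taken from T2 to T3, the wait list arm would be compared with people already treated, which is still not the comparison in the objectives.

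**Conclusion.** The point holds as one about the choice of contrast. No stated analysis answers the secondary objectives or supports a statement of potential effectiveness against no treatment. The T3 contrast falls after both arms have been treated, and the other two analyses have no concurrent control, although one is described as evaluating the intervention's effect.

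The structural finding needs no assumed numbers. It follows from the timing of T3 and the make-up of each analysis. The size, about 23% to 63% positive pooled anxiety tests against about 5% between arms, rests on the assumed drift of 0.2 to 0.3 SD, alpha 0.05, correlation 0.6 and 16 to 24 analysed per arm. It illustrates the risk and is not a forecast. It reflects bias from missing controls, which a multiplicity correction would not repair.

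The mismatch between one secondary outcome in the abstract and three in the main text is real but minor.

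**What to change.** In Statistical methods:

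1. Add the between-arm difference in GAI change from T1 to T2, with a confidence interval, and state that any statement about potential effectiveness rests on it alone.
2. Label the T3 between-arm contrast, the pooled pre-post analysis, the one-arm ANOVA, and the PSQI and MMQ results as exploratory estimates.
3. Reword the purpose of the pooled analysis: it describes change after EFMT, without a control.
4. Make the abstract agree with the main text and Objectives on the secondary outcomes.

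No multiplicity correction is needed.

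**Cost.** This is slightly more than a wording change, because it adds one between-arm analysis at T2. The data are already planned for all participants, so no visit or participant is added. The T2 calls to the wait list arm must precede its first session. This should be checked against the 7 to 10 day window under Comparators. The downside is that pre-post, sleep and memory results can no longer be presented as evidence of an effect, and that the T2 interval will be wide.
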